## 6.3. Combined treatment and supportive treatment

### 6.3.1. Acceptable combination and supportive care for hyperglycemia and hypoglycemia

Rescue treatments for hyperglycemia and hypoglycemia (as outlined in Section 6.1.3 Blood Glucose Management) are the only interventions permitted.

### 6.3.2. Other Acceptable Concomitant and Supportive Cares

The administration of medications used in routine clinical practice, including probiotics, antidiarrheals, and intravenous fluids, is permitted.

### 6.3.2. Unacceptable Concomitant and Supportive Therapy

There are no prohibited concomitant therapies or supportive treatments..

# 7. Anticipated Adverse Events

## 7.1. Expected Adverse Events and Defects

### 7.1.1. Adverse Events Associated with Enteral Nutrition (Meiji Main and Glucerna-REX ®)

1. Aspiration
2. diarrhea
3. constipation
4. Bloating
5. stomach ache
6. nausea
7. vomiting
8. Small bowel obstruction
9. Hyperglycemia
10. hypoglycemia

### 7.1.2. Adverse Events Associated with Esophagectomy

1. Postoperative pneumonia
2. Recurrent laryngeal nerve palsy
3. Anastomotic Leakage
4. Chylothorax
5. bleeding
6. Anastomotic stenosis
7. Delayed gastric excretion
8. Pancreatic fistula
9. Wound infection
10. Intra-abdominal abscess
11. Pleural effusion

### 7.1.3. Adverse Events Associated with the Use of FreeStyle Libre Pro

Serious adverse events at the site of sensor fitting

1. Local infections

Adverse events at the site of sensor attachment

1. bleeding
2. erythema
3. edema
4. rash
5. itch
6. Purpura
7. hardening
8. infection
9. pain
10. inflammation

### 7.1.4. Malfunctions Associated with the Use of FreeStyle Libre Pro

1. Malfunction of the software, errors when reading data or displaying information, etc. (Reader)
2. The power does not turn on/electrical system troubles (Reader)
3. Poor adhesion (sensor)

## 7.2. Evaluation of Adverse Events / Adverse Reactions

Adverse events associated with enteral nutrition will be evaluated using CTCAE ver. 5.0, and adverse events associated with esophagectomy will be evaluated using the Clavien Dindo classification.

## 7.3. Adverse Event Observation Period

Observation of adverse events will be performed for 30 days after the end of administration of Meiji Main and Glucerna-REX ®.

## 7.4. Causality Assessment

The causality between the observed adverse events and the administration of enteral nutrition products as well as the use of FreeStyle Libre Pro is determined as “related” when there is a reasonable temporal relationship between the occurrence of the adverse events and the administration of enteral nutrition products and the use of FreeStyle Libre Pro, and when the cause cannot be explained by factors other than the administration of enteral nutrition products and the use of FreeStyle Libre Pro.

Table 7.2.3 Criteria for Determining the Causality between Adverse Events and Treatment

| causal relationship | decision | Concept of judgment |
| --- | --- | --- |
| with | definite | Adverse events are apparent or severe due to protocol treatment and are judged to be unlikely to be due to exacerbation of the underlying disease or other factors |
|  | probable | Adverse events are unlikely to have arisen or become severe due to exacerbation of the underlying disease or other factors, and are likely to be due to protocol treatment. |
|  | possible | It is more plausible to assume that adverse events were caused or severed by protocol treatment, and are less likely to be due to exacerbation of the underlying disease or other factors. |
| without | unlikely | It was judged that it was more plausible to attribute adverse events to an exacerbation of the underlying disease or other factors than to assume that the adverse events were caused or severed by protocol treatment. |
|  | not related | Adverse events are clearly caused or severed by exacerbation of the underlying disease or other factors, and are judged to have little chance of protocol treatment |

# 8. Evaluation items

## 8.1. Endpoints prior to enrollment (within 28 days prior to the date of surgery)

1. Patient Background

Gender, date of birth, height, weight, blood pressure, pulse, anamnesis, complications, allergy history, medications used

1. Subjective symptoms, other findings, general condition PS (ECOG)
2. Peripheral blood count: leukocyte count, neutrophil count (ANC: rod nucleocytes + segmental nucleocytes), lymphocyte count, hemoglobin, platelets
3. Blood biochemistry: total protein, albumin, total cholesterol, total bilirubin, AST (GOT),

ALT (GPT), BUN, Creatinine, eGFR, LDH, Calcium, Sodium, Potassium, CRP, FBS (Fasting Blood Glucose), HbA1c, Prealbumin

1. Urinalysis (occasional urine): urine protein qualitative, urine glucose qualitative, urine specific gravity, urine pH, urine urobilinogen, urine bilirubin
2. X-ray, (contrast-enhanced) CT examination
3. Electrocardiography

## 8.2. Evaluation items on the day of surgery

1. Surgery Information
2. Allocation
3. FreeStyle Libre Pro attachement
4. 24-hour continuous glucose monitoring
5. Confirmation of Survival

## 8.3. Evaluation Items on Postoperative Day 1

1. Conformation of FreeStyle Libre Pro Continues
2. 24-hour continuous glucose monitoring
3. Blood glucose measurement 4 times a day with blood gas
4. Continuous administration of 400 mL of enteral nutrition (Meiji Main and Glucerna®-REX)
5. If necessary, the rescue of insulin for hyperglycemia and hypoglycemia
6. Presence or absence of postoperative infectious complications
7. Presence or absence of other complications
8. Adverse events
9. Confirmation of survival or death

## 8.4. Evaluation Items on Postoperative Days 2 to 3

1. Conformation of FreeStyle Libre Pro Continues
2. 24-hour continuous glucose monitoring
3. Blood glucose measurement 4 times a day with blood gas
4. Continuous administration of enteral nutrition (Meiji Main and Glucerna-REX ®) (postoperative day 2; 800 mL, postoperative day 3: 1200 mL)
5. If necessary, the rescue of insulin for hyperglycemia and hypoglycemia
6. Presence or absence of postoperative infectious complications
7. Presence or absence of other complications
8. Adverse events
9. Confirmation of survival or death

## 8.5. Evaluation Items on Postoperative Days 4 to 8

1. Conformation of FreeStyle Libre Pro Continues
2. 24-hour continuous glucose monitoring
3. Blood glucose measurement 4 times a day with dexter
4. Continuous administration of enteral nutrition (Meiji Main and Glucerna-REX ®) (postoperatively 4 days or later; 1600 mL)

Dosage may be changed or enteral nutrition may be changed depending on the patient's condition (e.g., adverse events) (see 6.2.3.)

1. If necessary, the rescue of insulin for hyperglycemia and hypoglycemia
2. Presence or absence of postoperative infectious complications
3. Presence or absence of other complications
4. Adverse events
5. Confirmation of survival or death

## 8.6. Evaluation Items on Postoperative Day 9

1. Remove the FreeStyle Libre Pro. (Postoperative 1~Collection of blood glucose data on day 8)
2. Enteral nutrition: Change of administration to Heinegel (change timing can be changed depending on the patient's condition)

However, if Meiji Main and Glucerna-REX ® are still administered after the 9th postoperative day, until the end of administration

## 8.7. Evaluation Items at Discharge: Acceptable discharge date±7 days

1. General Condition: PS
2. Peripheral blood count: leukocyte count, neutrophil count (ANC: rod nucleocytes + segmental nucleocytes), lymphocyte count, hemoglobin, platelets
3. Biochemical tests: total protein, total protein, albumin, total cholesterol, total bilirubin, AST (GOT), ALT (GPT), BUN, creatinine, eGFR, LDH, calcium, sodium, potassium, CRP, FBS (fasting blood glucose), HbA1c, prealbumin
4. Presence or absence of postoperative infectious complications
5. Presence or absence of other complications
6. Adverse events
7. Confirmation of survival or death

If discharge occurs later than 14 days after surgery, tests and evaluations should be conducted on postoperative day 14 as the discharge day.

## 8.8. Endpoints 30 days after the last dose of Meiji Main and Glucerna-REX ® (post-observation): acceptable + 14 days

1. Presence or absence of postoperative infectious complications
2. Presence or absence of other complications
3. Adverse events
4. Confirmation of survival or death

## 8.9. Study Calendar

|  | STUDY PERIOD | | | | | | | Close-out | |
| --- | --- | --- | --- | --- | --- | --- | --- | --- | --- |
|  | Enrolment | Allocation | Post-allocation | | | | |  |  |
|  |  |  | ICU | | | General ward | |  |  |
| TIMEPOINT | -28～-1 | 0 | 1 | 2 | 3 | 4～8 | 9 | At discharge | 30 days after the final dose |
| **ENROLMENT**: |  |  |  |  |  |  |  |  |  |
| Eligibility screen | X |  |  |  |  |  |  |  |  |
| Informed consent | X |  |  |  |  |  |  |  |  |
| Allocation |  | X |  |  |  |  |  |  |  |
| **INTERVENTIONS** |  |  |  |  |  |  |  |  |  |
| Meiji Main |  |  | X | X | X | X |  |  |  |
| Glucerna-REX ® |  |  | X | X | X | X |  |  |  |
| CGM |  | X | X | X | X | X | X |  |  |
| Intermittent blood glucose measurement |  |  | X | X | X | X |  |  |  |
| Dosage of enteral nutrition formula (mL) |  |  | 400 | 800 | 1200 | 1600 |  |  |  |
| **ASSESSMENTS**: |  |  |  |  |  |  |  |  |  |
| Infections cmplications |  |  | X | X | X | X | X | X | X |
| Other complications |  |  | X | X | X | X | X | X | X |
| Adverse effects |  |  | X | X | X | X | X | X | X |
| survival |  | X | X | X | X | X | X | X | X |

# 9. Reporting of Adverse Events

The reporting of adverse events shall be in accordance with the provisions of this chapter based on the "Clinical Trials Act" (Act No. 16 of 29), the "Enforcement Regulations of the Clinical Trials Act" (Ordinance No. 17 of the Ministry of Health, Labour and Welfare of Heisei 30), and related notices. "In the event of a serious adverse event ("illness" under the Clinical Trials Act), the co-investigator shall report it to the principal investigator/research office.

1. The severity criteria used for reporting adverse events are "7.2. Assessment of adverse events/adverse reactions" will be used.
2. Adverse events for which a causal relationship with this study cannot be ruled out are called diseases.
3. Diseases that occurred after the start date of protocol treatment and up to 30 days from the date of completion of protocol treatment are reported.
4. When reporting illness, etc., use the latest version of the form obtained from the Ministry of Health, Labour and Welfare website.

[**http://www.mhlw.go.jp/stf/seisakunitsuite/bunya/0000163417.html**](http://www.mhlw.go.jp/stf/seisakunitsuite/bunya/0000163417.html)

## 9.1. Adverse Events Subject to Reporting Requirements

Adverse events (including diseases) that meet any of the following criteria and for which causality with this study cannot be ruled out shall be subject to reporting.

Table 9.1　Reporting Obligation and Reporting Deadline

[figure not shown]

 **"Foreseeable: Unknown"** refers to those not listed in "7. Expected Adverse Events."

 **Death**: All deaths that occur after registration but before the initiation of protocol treatment, as well as all deaths that occur during protocol treatment or within 14 days from the date of treatment.

 **Life-threatening**: CTCAE Grade 4 events that occur during protocol treatment or within 14 days from the date of treatment.

 **Extension of hospitalization**: Events that occur during protocol treatment or within 14 days from the date of treatment.

※ "Hospitalization or extension of hospitalization" refers only to cases where hospitalization or an extension of hospitalization for 24 hours or more is medically necessary for the treatment of adverse events. The following cases are not subject to reporting:

- Hospitalization or extension of hospitalization for follow-up observation when the adverse event has resolved or improved.
- Hospitalization or extension of hospitalization to reduce the burden on the patient, such as in cases where the patient is coming from a remote area.
- Other hospitalizations or extensions of hospitalization that are not medically necessary.

.

## 9.2. Reporting Obligations and Procedures in the Event of Adverse Events or Diseases

### 9.2.1. Responsibilities of Personnel Engaged in This Study

Personnel engaged in this study must promptly report information regarding adverse events (including diseases) for which causality cannot be ruled out to the research office when they become aware of such events. However, reporting is not required if the adverse event is a progression (recurrence) of the underlying disease, a social hospitalization, or a hospitalization determined prior to participation in this study.

Even if the factors contributing to the occurrence of the adverse event are unclear, a preliminary report must be submitted based on the information available at that time. Subsequently, as soon as possible, the information that has been obtained up to that point should be documented and submitted as a follow-up report through the research office to the principal investigator. If it was initially determined that the causality could be ruled out but is later judged to correspond to a disease or other condition, the research office should be notified immediately at that point

.

### 9.2.2. Responsibilities of the Research Office

When the research office receives a report from personnel engaged in this study regarding the occurrence of an adverse event (including diseases) for which causality cannot be ruled out, it shall promptly provide a written report to the site administrator and the principal investigator.

### 9.2.3. Responsibilities of the Principal Investigator and the Research Secretariat

The principal investigator and the research office shall evaluate the urgency, significance, and impact of the reported disease or other conditions submitted to the research office, and take necessary measures such as temporarily suspending enrollment or issuing urgent notifications as needed.

### 9.2.4. Report to the Efficacy and Safety Evaluation Committee

If the principal investigator determines that an opinion from the Efficacy and Safety Evaluation Committee is required for a reportable adverse event, they shall promptly report the event to the committee and seek its opinion on the appropriateness of the principal investigator's perspective and the response to the adverse event.

### 9.2.5. Responsibilities of the Efficacy and Safety Evaluation Committee

The Efficacy and Safety Evaluation Committee will examine the details of the reported adverse events and make written recommendations to the principal investigator and the research office on measures to take, including whether or not to continue the study and whether or not to revise the protocol.

### 9.2.6. Report to the Accredited Clinical Research Review Board and the Minister of Health, Labour and Welfare

"Table 9.1) Refer to the "[Disease Report] Reporting Obligation and Reporting Deadline List", and if it is determined that the disease requires reporting, the report shall be made within the specified period.

**・Report to the Accredited Clinical Research Review Board**

Report to the Certified Clinical Research Board (CRB) using the "Pharmaceutical Disease Report (Unified Form 8)" and the "Detailed Description Form" stipulated in the Clinical Trials Act.

**・Report to the Minister of Health, Labour and Welfare**

Entering information into the "Disease Report" section of jRCT and sending an email to PMDA will serve as a report to the Minister of Health, Labour and Welfare

### 9.2.7. Periodic Reporting

The principal investigator shall report the occurrence of diseases to the CRB, the administrator of the medical institution, and the Minister of Health, Labour and Welfare in a periodic report conducted once a year on all diseases that have occurred in connection with clinical research.

# 10. Determination and endpoint definition

## 10.1. Evaluation items

**Primary endpoint**:

The average value of Time in Range (TIR) measured by Continuous Glucose

Monitoring (CGM) up to the second postoperative day.

**Secondary endpoints**:

1. Incidence rate of infectious complications during hospitalization

2. Incidence rate of infectious complications within 30 days postoperatively

3. Incidence rate of all complications during hospitalization

4. Incidence rate of adverse events

5. Average value of Time Above Range (TAR) during the entire measurement

period (postoperative days 1-8) measured by CGM

6. Daily TAR values measured by CGM up to postoperative day 8

7. Average value of Area Under the Curve (AUC) during the entire

measurement period

(postoperative days 1-8) measured by CGM

8. Daily AUC values measured by CGM up to postoperative day 8

9. Average value of Time in Range (TIR) during the entire measurement period

(postoperative days 1-8) measured by CGM

10. Daily TIR values measured by CGM up to postoperative day 8

11. Rate of change in nutritional indicators during hospitalization compared to

the time of admission (serum albumin, prealbumin, and total protein levels)

12. Number of cases requiring blood glucose control intervention for

hyperglycemia (≥ 300 mg/dL)

13. Number of cases requiring changes to enteral nutrition formulas from

postoperative day 3 onwards

14. Number of cases requiring a reduction of more than 50% in enteral

nutrition from the previous day after postoperative day 3y

# 11. Statistical Matters

Details of the statistical analysis are described in the statistical analysis plan to be prepared separately. For analyses that have been changed among the analyses planned by the protocol, the reason for the change shall be described in the statistical analysis plan.

## 11.1. Definition of Analysis Populations

The definition of the target population for this study is as follows. The handling of each case will be decided through consultation between the principal investigator, the research secretariat, the chief statistical analyst, and the data center before the data is fixed.

The efficacy analysis, including the main analysis, will be conducted in the Full Analysis Set (FAS), and the safety analysis will be performed in all treatment cases. The main analysis is a sensitivity analysis targeting the Per Protocol Set (PPS).

**・All Registered Cases**
All patients who have been registered are referred to as "All Registered Cases."

- **Full Analysis Set (FAS)**
   The group derived from the "All Registered Cases" after excluding patients with significant eligibility criteria violations, patients who violated exclusion criteria, patients who did not receive any protocol treatment, patients with no efficacy-related data, and patients who withdrew consent and refused to allow the use of any data. This group is defined as "FAS."
- **PPS (Per Protocol Set)**
   The group derived from the "FAS" after excluding patients who discontinued protocol treatment by the second postoperative day or had significant protocol violations is defined as "PPS."
- **All Treated Cases**
   Patients who received part or all of the protocol treatment are referred to as "All Treated Cases".

## 11.2. Handling of Missing Data

As a general rule, missing data will not be imputed. However, if necessary, analyses with imputed missing data will be conducted as sensitivity analyses. Details on the handling of missing data will be described in the statistical analysis plan. If the sensor detaches for any reason during the ICU stay, resulting in missing data, a sensitivity analysis will also be performed on cases where the data collected from the time the sensor was attached until the time it detached covers 70% or more (6.3 days or more) of the planned measurement days, based on the previously reported recommendations [8, 12].

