### 2.3.3. FreeStyleLibre Pro

The FreeStyle Libre Pro used in this study includes a blood glucose monitoring sensor and a Reader (Figure 1). Typically, the sensor is applied to the outer upper arm to ensure comfort and ease of movement. It should be placed avoiding areas with scars, moles, stretch marks, lumps, or sites used for insulin injections. In this study, once the patient returns to the ward immediately after surgery, a sub-investigator will attach the sensor to the outer upper arm of the patient and conduct continuous blood glucose monitoring from postoperative day 1 to day 8. On postoperative day 9, data will be extracted using the dedicated Reader through a scanning procedure, after which the sensor will be disposed of.

It should be noted that during routine postoperative X-ray examinations, it is not necessary to remove the sensor.

**Figure 1: Continuous blood glucose meter (CGM) used in this study: FreeStyle Libre Pro (Abbott Japan)**（<https://www.myfreestyle.jp/hcp/>）

[figure not shown]

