2.4.1. Blood glucose measurement using CGM

To verify the effects of the glucose-restricted enteral formula Glucerna®-REX, the following parameters obtained from CGM will be evaluated as indicators of its ability to suppress blood glucose elevation.

Primary outcome：

**TIR (Time in Range)**: Defined as the percentage of time during 24-hour continuous blood glucose monitoring in which blood glucose levels are within the target range of 70-180 mg/dL (the time period when the curve is within the red box in Figure 2 (hours)/24h).

Secondary outcomes：

**Time Above Range (TAR)**: Defined as the percentage of time during 24-hour continuous blood glucose monitoring in which blood glucose levels are ≥180 mg/dL, representing the hyperglycemic range (the sum of time periods labeled as ① in Figure 2 (hours)/24h) [7].

**Area Under the Curve (AUC)**: Defined as the area under the curve for blood glucose levels ≥180 mg/dL during 24-hour continuous blood glucose monitoring, representing the extent of hyperglycemia (the sum of the shaded areas labeled as ② in Figure 2) [9].

TIR (Time in Range) was introduced as a new glycemic control indicator in the "International Consensus on Glycemic Control Targets" presented at the American Diabetes Association (ADA) Scientific Sessions in June 2019 [8]. This indicator has been shown to correlate with conventional glycemic control markers, such as HbA1c, with a 10% increase in TIR being associated with an approximate 0.5% decrease in HbA1c (Figure 2) [9]. Additionally, TIR has the advantage of detecting hidden hyperglycemia and hypoglycemia that cannot be captured through intermittent measurements, making it a precise and comprehensive indicator. Given these attributes, TIR has been deemed an appropriate primary endpoint for this study.

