### 6.2.2. Criteria for Protocol Treatment Discontinuation

Protocol treatment will be discontinued in any of the following situations. The date of protocol treatment discontinuation will be defined as the date of death in the event of death or the date on which the attending physician determines that protocol treatment should be discontinued for other reasons.

When it becomes difficult to continue the study due to adverse events.

1. If the patient offers to discontinue protocol treatment.
2. Death during protocol treatment
3. When it is determined that discontinuation is necessary at the discretion of the principal investigator or co-investigator.
4. During the ICU period (within 4 days after surgery), the sensor is removed and the missing data is revealed.
5. By the second postoperative day, hyperglycemia (300 mg/dL or more) requiring insulin administration.
6. By the second postoperative day, the patient has a hypoglycemic condition (69 mg/dL or less) that requires sugar administration.
7. Skin troubles attributed to the FreeStyle Libre Pro sensor adhesive.
8. The need arises to remove the seal on the FreeStyle Libre Pro sensor for an MRI examination.
9. In addition, if serious deviations from the protocol are discovered, such as protocol violations, post-registration surgical procedures, or changes in treatment policies.

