## 11.3. Main Analysis

In this study, the primary analysis will focus on the average Time in Range (TIR) measured by CGM (Continuous Glucose Monitoring) up to the second postoperative day, which is the primary endpoint to be evaluated after patient enrollment is complete. Using analysis of covariance (ANCOVA), the adjusted mean difference in the primary endpoint between the two groups (intervention group - control group) will be calculated along with the 95% confidence interval and standard deviation. Additionally, as a reference, the p-value for the null hypothesis that the mean difference between the two groups is zero will be provided, along with the mean value (least-squares mean) and its 95% confidence interval and standard deviation for each group, including the results without adjusting for allocation factors. The average TIR up to the second postoperative day is defined as the proportion of time within the 48-hour period where blood glucose is within the therapeutic range of 70-180 mg/dL.

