## 11.4. Sub-evaluation projects (efficacy).

For the following items, calculate the mean values and the corresponding 95% confidence intervals and standard deviations for each group and the intergroup difference (intervention group - control group). If necessary, calculate the p-values using Welch's t-test for comparisons between the two groups.

- Average TAR (Time Above Range) over the entire measurement period (Postoperative Day 1 to Day 8) measured by CGM
- Daily TAR up to Postoperative Day 8 measured by CGM
- Average AUC (Area Under the Curve) over the entire measurement period (Postoperative Day 1 to Day 8) measured by CGM
- Daily AUC up to Postoperative Day 8 measured by CGM
- Average TIR (Time in Range) over the entire measurement period (Postoperative Day 1 to Day 8) measured by CGM
- Daily TIR up to Postoperative Day 8 measured by CGM

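### The 70% (6.3-day) coverage rule for sensors lost in the ICU cannot be met on the scheduled ICU stay, and its day count disagrees with the stated eight-day measurement period

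*Protocol*

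**What the plan says.** Section 11.2 of the protocol fixes three elements of one sensitivity analysis.

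- The trigger: "If the sensor detaches for any reason during the ICU stay, resulting in missing data, a sensitivity analysis will also be performed".
- What counts towards coverage: "the data collected from the time the sensor was attached until the time it detached".
- The threshold: the record must be one that "covers 70% or more (6.3 days or more) of the planned measurement days".

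The same section says that missing values are in general not imputed, allows imputation-based sensitivity analyses where needed, and leaves details to the SAP.

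Other sections supply the durations.

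- **Measurement period.** Section 2.3.3 plans to "conduct continuous blood glucose monitoring from postoperative day 1 to day 8", and Section 11.4 averages the secondary glucose measures "over the entire measurement period (Postoperative Day 1 to Day 8) measured by CGM".
- **Sensor wear.** Section 6.1.3 has the sensor attached on return from surgery and removed on postoperative day 9. Section 8.2 and the calendar in Section 8.9 list glucose monitoring from day 0.
- **ICU stay.** The tables in Sections 2.2.2 and 8.9 place the patient in the ICU on days 1 to 3 and in the general ward from day 4. Section 6.2.2 words it differently: "During the ICU period (within 4 days after surgery), the sensor is removed and the missing data is revealed".
- **Endpoint windows.** Section 11.3 states: "The average TIR up to the second postoperative day is defined as the proportion of time within the 48-hour period". Section 2.4.1 gives daily time in range (TIR) as "the time period when the curve is within the red box in Figure 2 (hours)/24h".

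**The concern.** A coverage rule should separate records long enough to analyse from those that are too short. This one admits only patients whose sensor was lost early, and then asks them for more data than an early loss can leave. If the condition is out of reach on the scheduled ICU stay, the analysis has no patients of the kind it was written for.

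Two further points add to this. The number of days beside the percentage does not match the stated measurement period, so a patient with between 5.6 and 6.3 days of data passes on one count and fails on the other. The rule also measures the whole record, while the primary endpoint uses only the first two postoperative days. It therefore says nothing about whether the primary outcome was adequately observed.

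**Working it through.** **1. The protocol's own figure.** The inputs are 70% and 6.3 days, both from Section 11.2.

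- 6.3 / 0.70 = 9.0 planned days. Nine days fits wear on days 0 to 8 (attachment on day 0, removal on day 9).
- On the stated eight days (postoperative days 1 to 8), 0.70 × 8 = 5.6 days.
- 6.3 / 8 = 78.75%, so on eight days the stated figure is not 70%.

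**2. Can a sensor lost in the ICU reach 70%?** Coverage = longest possible wear at an ICU detachment / planned days.

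| Longest wear | Basis | Of 8 days | Of 9 days |
| --- | --- | --- | --- |
| 4 days | day 0 to the end of day 3 (tables in Sections 2.2.2 and 8.9), or 4 elapsed days (Section 6.2.2) | 4/8 = 50% | 4/9 = 44% |
| 5 days | day 0 to the end of day 4 (most generous reading of Section 6.2.2) | 5/8 = 62.5% | 5/9 = 56% |

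Every entry is below 70%. The eight-day column is generous, because it credits day 0 in the numerator although day 0 lies outside postoperative days 1 to 8. To qualify, the sensor must come off in the ICU after at least 5.6 days (eight-day count) or 6.3 days (nine-day count).

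**3. Whole record against primary window.** Take a patient with complete data on postoperative days 1 and 2 whose sensor comes off on day 3.

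- Primary window observed: 48/48 h = 100%.
- Whole record: at most 4 days, that is 50% of 8 or 44% of 9, so the patient fails.
- The same 70% applied to the primary window would be 0.70 × 48 = 33.6 h.

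**4. Literal denominators (supporting point only).** If lost time earns no in-range credit and the divisor stays at 48 h, then reported TIR = observed in-range share × observed hours / 48. The in-range shares and hours lost below are assumptions; the protocol gives neither.

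- 60% in range, 6 h lost: 0.60 × 42/48 = 52.5%, a fall of 7.5 points in that patient. With 24 patients in an arm (half of the planned 48), the arm mean moves by 7.5/24 = about 0.3 points.
- In-range shares of 50 to 90%, 12 h lost: a fall of 12.5 to 22.5 points in that patient, or 0.5 to 0.9 points in the arm mean.
- In-range shares of 50 to 90%, 24 h lost: a fall of 25 to 45 points, or 1.0 to 1.9 points in the arm mean.

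For scale, the planned precision reproduces if the 8.5% is read as a per-patient standard deviation: t(0.975, 46) × 8.5 × √(2/24) = 4.94, against the stated ±5 points. One partial record per arm is small beside that. The same literal formula would lower time above range (TAR) too.

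**The case against.** **Nine days is defensible.** Section 11.2 speaks of planned measurement days without tying them to postoperative days 1 to 8, and monitoring is listed from day 0. This stands. The 6.3 is not a proven slip of arithmetic. It is a conflict between two counts that the protocol uses.

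**A long ICU stay could qualify.** This also stands. It would be wrong to say that no patient at all can meet the rule; the statement holds for the scheduled stay. Nor is the set necessarily empty if the rule is read as admitting every patient with at least 70% coverage. Even so, it would leave out every sensor lost on the scheduled ICU stay.

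**Details belong to the SAP.** This stands only in part. The protocol itself fixes the trigger, the percentage and the number of days. An SAP that follows them inherits an unusable condition, and one that repairs them departs from the protocol.

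**Other analyses deal with missing data.** This is correct. Section 11.2 allows imputation-based analyses. Section 11.1 adds a per-protocol sensitivity analysis that leaves out patients who discontinued by postoperative day 2, and Section 6.2.2 makes ICU sensor loss with missing data a reason for discontinuation. The defective rule is not the only protection.

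**Lost time as out of range.** A reader might infer from the 24-hour and 48-hour denominators that the protocol scores lost sensor time as out of range. It nowhere says so. Those definitions can equally describe a fully observed window, and the general rule is not to impute. A reader might also infer that a patient with a long gap in the first 48 hours who wears the sensor to day 9 passes the rule. That patient's sensor did not detach in the ICU, so the rule does not apply.

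**Conclusion.** The point holds for the rule in Section 11.2. On the scheduled ICU stay, a sensor lost there supplies at most 50 to 62.5% of eight days or 44 to 56% of nine, so the 70% condition is out of reach under either count and under both descriptions of the ICU period. The eight-day and nine-day counts must be reconciled, since they place the threshold at 5.6 or 6.3 days. The threshold also looks at the wrong window for the primary endpoint, rejecting patients whose 48 hours are complete.

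The conclusion assumes that coverage runs from attachment to detachment, as written, and that the ICU stay follows the schedule.

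A reader might go further and conclude that the primary result is biased. The documents do not support that. They give no frequency of sensor loss, no imbalance between arms and no stated scoring of lost time. The trial is described as hypothesis-generating (Section 2.6), and its p-value is for reference only (Section 11.3). This should be fixed, but the main analysis in the full analysis set is not shown to be wrong.

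**What to change.** In Section 11.2:

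- State the number of planned measurement days once, with the matching threshold for the postoperative day 1 to 8 endpoints: 5.6 of 8 days or 6.3 of 9 days. If nine is kept, say that day 0 counts.
- For the primary endpoint, apply the 70% to the 48-hour window (33.6 h). This carries over the protocol's own percentage; it is not a separately justified cut-off.
- Apply the rule to sensor loss at any time, not only in the ICU.

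As a supporting clarification in Sections 2.4.1 and 11.3, state that TIR and TAR are computed over valid sensor time, so that the fixed denominators cannot be read as giving lost hours no credit.

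The cost is wording in these three sections, carried into the SAP before the data are fixed. No extra data are needed.
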